## Abstract

**Background:**

The model of Family group-conferencing (FG-c) for decision making in child welfare has rapidly spread over the world during the past decades. Its popularity is likely to be caused by its philosophy, emphasizing participation and autonomy of families, rather than based on positive research outcomes. Conclusive evidence regarding the (cost) effectiveness of FG-c is not yet available. The aim of this protocol is to describe the design of a study to evaluate the (cost) effectiveness of FG-c as compared to Treatment as Usual.

**Method/Design:**

The effectiveness of FG-c will be examined by means of a Randomized Controlled Trial. A multi-informant approach will be used to assess child safety as the primary outcome, and commitment of the social network, perceived control/ empowerment; family functioning and use of professional care as secondary outcomes. Implementation of FG-c, characteristics of family manager and family will be examined as moderators of effectiveness.

**Discussion:**

Studying the effectiveness of Fg-c is crucial now the method is being implemented all over the world as a decision making model in child and youth care. Policy makers should be informed whether the ideals of participation in society and the right for self-determination indeed result in more effective care plans, and the money spent on FG-c is warranted.

**Trial registration:**

Dutch Trial Register number NTR4320. The design of this study is approved by the independent Ethical Committee of the Faculty of Social and Behavioral Sciences of The University of Amsterdam (approval number: 2013-POWL-3308). This study is financially supported by a grant from ZonMw, The Netherlands Organization for Health Research and Development, grant number: 70-72900-98-13158.

## Background

The model of Family group-conferencing (FG-c) for decision making in child welfare has rapidly spread over the world during the past decades [1]. Also in the Netherlands, Family Group conferences are widely used as a decision making procedure in youth care [2]. Research has indicated, however, that its popularity is likely to be caused by its philosophy (emphasizing participation and autonomy for families), rather than based on research outcomes showing positive results for FG-c [3,13]. The question is whether FG-c’s in youth care yield what they are developed for: increased child’s safety (i.e., decrease in (risk for) abuse/neglect, less supervision orders or shorter supervision order, less or shorter out of home placement), involvement of the broader social network; perceived control over the problems in the families, empowerment of parents; improvement of family functioning, and less use of professional care.

Despite the broad implementation of FG-cs globally and despite many research efforts into FG-c, Frost et al. (2012) concluded that it is not possible to draw conclusions about the effectiveness of FG-cs because there is a lack of robust research allowing causal inferences, i.e., few (quasi) experimental or longitudinal studies have been conducted [1]. Studies tend to mainly focus on the implementation of the conferences and of the Family Group plans, and on participant satisfaction. In a study by Oosterkamp-Szwajcer et al. (2012), the majority of the participants indicated that the situation had improved after a FG-c, in 87% of the families the plans were carried out at least partially, and the family felt empowered [4]. However, given that no comparison group was included in this study, these positive results cannot be attributed to FG-c. In another Dutch study, Schuurman (2011) concluded that FG-c in 95% of the cases resulted in a plan, that participants were satisfied and that the situation had improved [5]. Schuurman and Mulder ( 2011) and Jagtenberg et al. (2011) argue that FG-cs save costs that otherwise would be spent on professional care [6,7]. Also in the research report provided by WESP (2008) all FG-cs resulted in a plan which, according to 44% of the members of the social network, was completely carried out [8]. None of these studies, however, used a comparison group, and thus results cannot with certainty be attributed to the use of FG-cs.

Research that did include a (not in all respects equivalent) comparison group [9], found that families that had participated in a FG-c reported less concerns about safety and well-being of the children and that social support from the network had increased. However, the changes in the Family Group-conferencing group were not larger than in the control group, and several methodological flaws of the study (e.g., short follow-up time, non-equivalence of the experimental and control group, high drop-out rates, lack of statistical power, and inadequate statistical analyses) did impose significant limitations on the causal inferences that could be drawn.

Notably, studies examining FG-cs show inconsistent results. Some researchers found positive effects of FG-c’s on short-term but no long-term effectiveness [10]. Where Burford et al. (2013) reported positive results of FG-c, Lorentzen (2009) and Sundell et al. (2004) did not find evidence for the effectiveness of FG-c’s [11-13]. Berzin et al. (2008) reported negative outcomes: families who had participated in FG-c had adverse outcomes for safety and stability of out of home placements and frequently refused necessary youth care [14]. A recent systematic review including only controlled studies, of which only six were available, showed that FG-c’s lead to an increase in child abuse, more and longer out of home placements and ultimately to an increase in use of professional care [15].

To conclude, although much research has been done to investigate FG-cs, there is still insufficient evidence for its effectiveness, in particular because of the use of weak study designs [16]. Research with a robust design does not confirm the positive findings reported in the uncontrolled studies [15]. Worldwide, only six studies including a control group have been conducted. It is therefore crucial to conduct a study that allows for conclusions on causality about the effects of FG-c’s.

Even less is known about potential moderators of the effectiveness of FG-cs: in which families, under what circumstances will family group conferences have the best results? Effectiveness studies try to find overall effects, whereas not all families are likely to benefit from one approach [17]. As Farrell, Meyer, Kung, and Sullivan (2001, p. 216) stated, “one cannot assume that an intervention program is equally effective with all participants” [18]. Therefore, analysis of overall program effects might suggest that programs did not work when in fact they did work for some subgroups [19]. Identifying moderators of the intervention effectiveness can be useful for identifying and engaging those who are most likely to benefit [20], and provides opportunities to adjust the programs to improve effectiveness for certain subgroups of clients.

In addition to potential moderating effects of family characteristics, program integrity may also moderate the effectiveness of FG-cs. An FG-c starts off with an initializing stage, than the actual conference takes place, and subsequently, the Family Group plan needs to be carried out. It is important to determine whether all stages belonging to a FG-c are carried out and to what extent the Family Group plan has been carried out as intended. This information can be used to determine which stages of the FG-c are critical for the achievement of potential positive results.

To increase the knowledge about the effectiveness of Family Group Conferences in youth care, we will perform a randomized controlled trial (RCT). In contrast to previous research that had several methodological shortcomings, this study will provide the opportunity to draw (scientifically robust) conclusions about the effectiveness of FG-c’s. In addition, it will become clear which characteristics of the approach, of the participating families and which characteristics of the family managers who should support the implementation of the Family Group plans are important to reach the best results. Finally, in times in which large amounts of public money are spent on ‘family autonomy and participation in child care’, operationalized in Family Group Conferences, it is important to base policy decisions concerning whether or not to continue those investments on clear numbers regarding the costs and benefits of Family Group Conferences. Therefore, the present effectiveness study will be accompanied by a cost-effectiveness analysis.

## Methods and design

The study aims to answer two main questions. The first question is whether Family Group conferences in youth care are effective as a decision making model in terms of increased child safety, involvement of the social network, perceived control over problems and a reduction in use of professional care. In order to determine the effectiveness of FG-cs, a RCT will be carried out including 300 families referred to Youth Care Agency Amsterdam (YCAA). Moreover, costs associated with FG-c will be identified in order to determine the cost-effectiveness of FG-cs.

The second research question concerns the moderators of the effectiveness of FG-c. Both participant and program characteristics will be examined as potential moderators. Program characteristics to be examined are program integrity and characteristics of FG coordinators and family managers (responsible for supporting the implementation of the FG plans developed by the broader social network of the family). It is crucial to examine program integrity (i.e., the extent to which different phases of a FG-c have been conducted according to the protocol). Without having established program integrity, there is the risk of concluding that FG-cs are not effective, whereas in fact the FG-c has not been fully implemented. Furthermore, it is possible that a successful FG-c has taken place, but the plan developed in the FG-c has never been carried out. It is therefore important to determine whether all stages of the FG-c have been implemented as planned.

Additionally, it is important to examine family characteristics as potential moderators of the effectiveness of FG-c. It is plausible that FG-cs are not equally effective for every participating family. For example, families with a small social network, or with limited possibilities to attend a conference or with other particular characteristics that hamper the organization or carrying out of a FG-c or the FG plans are less likely to attend a FG-c. Identifying those families who are less likely to fulfill an FG-c may result in savings.

### Design

A randomized Controlled trial will be conducted to examine whether FG-cs are effective in changing: (1) child’s safety (i.e., decrease in (risk for) abuse/neglect; less supervision orders or shorter supervision order; less or shorter out of home placement); (2) the involvement of the broader social network; (3) perceived control over the problems in the families, empowerment of parents; improvement of family functioning; (4) less use of professional care. A second aim is to study whether the effectiveness of FG-c is influenced by characteristics of the implementation of the methodology, characteristics of the family managers (such as education, or attitude towards FG-c), or by family characteristics (such as size of the social network, ethnicity or family type: single/married).

Using computerized randomization two comparable groups will be formed. Until the inclusion of 300 families is completed (presumably within 6 months), every family starting care at Youth Care Agency Amsterdam (YCAA) will be randomly allocated to care with or without a Family Group conference. Because allocation to care with a FG-c will not always result in an actual Family Group conference and/or an approved Family Group plan, 200 families will be assigned to care with FG-c and 100 families to care without FG-c. Five multi-informant/source (parent, family manager; FG-coordinator; member of the family’s social network; child (if > 8 years of age), and file analysis) assessments will be carried out in both groups. Pre-tests will take place before FG-cs starts. Subsequently, in both groups post-tests will be carried out 1, 3, 6 and 12 months after the FG-c has taken place (see also Figure 1 for the flow chart).

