### Recruitment

Participants are recruited at Youth Care Agency Amsterdam and Surroundings (YCAA). When a family is referred to YCAA, a first step is to establish whether the family indeed belongs to the target group of YCAA. If that is the case, a YCAA manager determines whether the need for help is urgent. If this is the case, the family is immediately assigned to a personal family manager and is informed about the study. In this stage, randomization takes place, active informed consent is received and both youth care and the study will start. If the situation is less urgent, families may be placed on the waiting list. For those families, informed consent, randomization and start of youth care will be postponed until the waiting list period has expired. Specifics on the flow of participants are graphically presented in Figure 1.

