### Moderators

*Characteristics of the Family Group-conferences (FG-c)*, such as number of families per FG-coordinator, location, time to start of FG-c, number of members of the network present at the FG-c, will be registered on the registration form developed for this specific study.

Additionally, specific characteristics of the Family Group-conference, related to the *implementation of the FG-c*, will be registered on this form too, such as whether the separate phases of the FG-c have been followed as intended, duration of these phases, and whether the plan is carried out as intended and who was responsible for the carrying out of the plan, and whether this person took the assigned role.

Moreover, the *role of the family manager* in the carrying out of the FG-c will be monitored with the registration form: did the family manager bring the FG-c up within the intended period of time (2-6 weeks after start)? Was the family manager supportive of FG-c (and why (not))? Did the Family manager leave control with the family (and why (not))?

*Characteristics of the families* that may affect the effectiveness will be assessed. Demographics will be coded from the file research and information that is not present in the YCAA file will be asked with a questionnaire. Risk factors will be assessed with a risk list that consists of a combination of the Washington Prescreen Risk Assessment instrument [35], for the penal law cases and the Delta risk list specifically developed for civil law cases.

*Problems of the child* will be assessed with the Brief Problem Checklist [36], to be filled out by the parents (if the child is younger than 8 years of age) or the child (if the child is older than 8). This is a validated short questionnaire that assesses problems of the child.

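### All post-tests are dated from the conference, a date that no control family and not every FG-c family will have, so the assessments for the intention-to-treat analysis cannot be scheduled as written

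*Protocol article*

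**What the plan says.** The Design section sets the assessment schedule in one sentence: "Subsequently, in both groups post-tests will be carried out 1, 3, 6 and 12 months after the FG-c has taken place". Just before it, the section gives the allocation, "200 families will be assigned to care with FG-c and 100 families to care without FG-c", and the reason for the 2:1 ratio: "Because allocation to care with a FG-c will not always result in an actual Family Group conference and/or an approved Family Group plan". For the baseline it says only: "Pre-tests will take place before FG-cs starts".

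The text that follows Figure 1 in the same section again counts the 1-, 3- and 6-month post-tests from the conference when it describes the checks on whether the plan was carried out. The note to Table 1 (Instruments) lists T2 to T5 at 1, 3, 6 and 12 months and names no starting point.

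Recruitment places randomisation and the start of the study at the start of care: "In this stage, randomization takes place, active informed consent is received and both youth care and the study will start". Moderators gives the only documented delay between that start and the conference. It asks of the family manager: "did the family manager bring the FG-c up within the intended period of time (2-6 weeks after start". It also lists "time to start of FG-c" among the characteristics to be recorded, so the delay is expected to vary. Conditions describes a preparation phase before the meeting and gives it no duration.

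Statistical analyses plans an intention-to-treat and a completer analysis. Missing data are imputed so that everyone is included, and the comparison is an ANCOVA of each post-test adjusted for its pre-test.

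**The concern.** The anchor is an event after randomisation that one arm lacks by design and part of the other arm is expected to lack. Applied literally, the rule gives those families no post-test date. This is more than a detail left to a fuller document: a rule is stated for both groups, and it cannot be applied to either group in full.

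Two things are at stake. First, the data for the intention-to-treat comparison depend on dates that someone will have to improvise. Imputation does not solve this, because if the rule were followed literally there would be no observed control post-tests from which to impute. The FG-c families without a conference are also unlikely to be a random subset: Methods and design itself expects families with small networks or limited ability to attend to take part less often.

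Second, the obvious improvisation for controls is to count from randomisation or start of care, which would put the two arms at different distances from randomisation at every nominally equal visit. If safety changes with time in care, part of that difference would appear in the treatment contrast.

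**Working it through.** **The plan's own figure.** Study sample gives 300 families at 2:1, alpha .05 and d = .35, with no power figure. I assume a two-sided test and 80% power. The control group needed is (1 + 1/2)(1.960 + 0.842)² / 0.35² = 1.5 × 7.85 / 0.1225 = 96.1, rounded up to 97. With 194 in the FG-c arm the total is 291, against 300 stated. With 100 and 200 families, 0.35 / √(1/100 + 1/200) = 2.858, so power is Φ(2.858 − 1.960) = 81.5%. The sample size reproduces, and the timing point does not depend on it.

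**Families without a date under the stated rule.** Undated = 100 controls + 200 × p, where p is the share of the FG-c arm without a conference (not given, so assumed).

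- p = 10%: 100 + 20 = 120 of 300 (40%)
- p = 25%: 100 + 50 = 150 of 300 (50%)
- p = 50%: 100 + 100 = 200 of 300 (67%)

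**Elapsed time if controls are dated from start of care.** This control clock is an assumption. One month is 52.18 / 12 = 4.35 weeks. Controls are tested k × 4.35 weeks after start. FG-c families are tested at d + k × 4.35 weeks, where d is the delay to the conference. Taking d as only the 2-6 weeks intended for raising it, with no preparation time, gives:

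| Nominal test | Controls (weeks) | FG-c, d = 2 to 6 (weeks) | Ratio |
|---|---|---|---|
| 1 month | 4.3 | 6.3 to 10.3 | 1.46 to 2.38 |
| 3 months | 13.0 | 15.0 to 19.0 | 1.15 to 1.46 |
| 6 months | 26.1 | 28.1 to 32.1 | 1.08 to 1.23 |
| 12 months | 52.2 | 54.2 to 58.2 | 1.04 to 1.11 |

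If preparation takes 0-8 weeks (assumed), the gap becomes 2-14 weeks, and the FG-c 1-month test can be up to 4.2 times as far from start as the control test.

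**Conversion to effect size.** Assume a linear improvement of 0.5 SD a year under usual care. The documents give no such figure. The spurious difference is 0.5 × d / 52.18:

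- d = 2 weeks: 0.019 SD, and 0.019 / 0.35 = 5%
- d = 6 weeks: 0.057 SD, and 0.057 / 0.35 = 16%

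The result is proportional to the slope. It halves at 0.25 SD a year, vanishes if usual care brings no change, and reverses sign if families get worse.

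**The case against.** The strongest reply is that the article is condensed. The schedule sentence points to Figure 1, which is not shown here, and control dates may be set there or in a fuller protocol. A control date matched to the expected conference delay would fit the wording and could remove the average gap between arms. This stands to the extent that unequal timing is not demonstrated. It does not rescue the sentence, which gives both groups one anchor that many families lack and would need correcting whatever the figure shows.

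A reader might go further and infer that the randomised comparison is lost. The documents do not support that. Statistical analyses keeps every participant in, and Design records whether a conference took place, which implies that families without one are still followed. A date chosen ad hoc adds noise or bias, but families can still be analysed as randomised.

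A reader might also infer that urgent families are randomised before they consent, because Recruitment names randomisation first for them and, for waiting-list families, says "For those families, informed consent, randomization and start of youth care will be postponed until the waiting list period has expired". Both sentences list what happens at a stage and set no order. Likewise, a pre-test taken with the arm already known is possible under the wording but is nowhere stated. The requirement that it precede the FG-c can be read as preceding the preparation phase too.

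Finally, a larger bias is easy to produce. A 2-month lag with the same slope gives 0.5 / 12 × 2 = 0.083 SD, or 24% of d = .35. That lag is not documented; only the 2-6 weeks are.

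**Conclusion.** The point holds as a defect in a stated rule. T2 to T5 are tied to a date that all 100 controls and an unstated number of the 200 FG-c families will not have, so the post-tests for the planned intention-to-treat analysis cannot be dated as written. This follows from the text and needs no assumption. It affects every post-test, including those of the primary outcome, and should be corrected.

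The bias is conditional. If controls are dated from randomisation or start of care, and usual care improves outcomes by 0.5 SD a year, the documented 2-6 weeks correspond to about 0.02-0.06 SD in favour of FG-c (5-16% of d = .35), and preparation time would add to this. In relative time the distortion is greatest at 1 month and modest at 12 months (4-11%). That the arms will in fact be measured at different times is not established, because no control date is given.

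**What to change.** In Design, time T2 to T5 at 1, 3, 6 and 12 months after randomisation in both arms, whether or not a conference is held. Every randomised family has that date. Keep the time to conference, which is already to be recorded, as a process variable. Tie the checks on plan implementation to the conference date separately, for families that held one. State in the same place that the 6- and 12-month tests carry the effectiveness comparison. As a secondary clarification, say that T1 is completed before the allocation is disclosed.

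The change needs rewording and rescheduling, and no extra families; with 300 families dated, power stays at about 81.5% under the assumptions above. It has a real cost. The 1-month test, at 4.3 weeks, falls inside the 2-6 week window for raising the conference and so will precede or coincide with many conferences. The 3-month test may do so for some: a conference raised at week 6 with 8 weeks of preparation (assumed) is held at week 14, after the test at week 13.0. Both then describe early process more than the effect of a completed conference. The implementation checks also need their own calendar. Table 1 takes them from the family manager, the coordinator and the researcher, so this need not add contacts with families.

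A control date matched to the conference delay is an alternative. It would have to be defined in advance, and would also have to cover FG-c families without a conference.
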